## Abstract

**Introduction:**

Chronic musculoskeletal (bone, joint or muscle) pain is disabling. People with it frequently have difficulties in managing everyday activities. Individuals may rely on family members or friends to support them. These people are known as informal caregivers. No interventions have previously addressed the health needs of people with chronic musculoskeletal pain and their caregivers. In response, the JOINT SUPPORT programme was developed. In this study, we will assess the feasibility and acceptability of conducting a pragmatic, multicentre, randomised controlled trial (RCT) to test the clinical and cost-effectiveness of the JOINT SUPPORT programme to support these individuals.

**Methods and analysis:**

This will be a mixed-methods feasibility RCT. We will recruit 80 patients with chronic musculoskeletal pain with their informal caregivers. Patients will be randomised to usual National Health Service (NHS) care *OR* usual NHS care plus a caregiver–patient dyad training programme (JOINT SUPPORT). This programme comprises of five, 1-hour, group-based sessions for patients and caregivers, delivered by trained physiotherapists or occupational therapists. It includes developing skills in: understanding pain, pacing, graded activity, fear avoidance and goal-setting, understanding benefits of physical activity and skills in medication management. This will be re-enforced with a workbook. After the group-based sessions, patients and caregivers will be supported through three telephone sessions with a therapist. Data collected at baseline and 3 months will include: screening logs, intervention logs, fidelity checklists and clinical outcomes on quality of life, physical and emotional outcomes, adverse events and resource use. Qualitative research with 24 patient–caregiver dyads and 12 healthcare professionals will explore the acceptability of trial processes. Stop–go criteria will inform the progression to a full trial.

**Ethics and dissemination:**

Ethical approval was obtained on 22 February 2022 (National Research Ethics Committee Number: 22/NW/0015). Results will be reported at conferences, peer-review publications and across social media channels.

**Trial registration number:**

ISRCTN78169443.

Strengths and limitations of this studyJOINT SUPPORT is a pragmatic, multicentre, feasibility randomised controlled trial (RCT).This study will determine if it is feasible to conduct an RCT to assess the effectiveness of a caregiving intervention for people with chronic musculoskeletal pain.The sample size is sufficient to inform decision-making on the design of a larger full-trial.The embedded qualitative study will explore experiences and views on the study design and intervention.The relatively small sample size increases the risk of higher potential loss to follow-up.

## Introduction

Chronic musculoskeletal (bone, joint or muscle) pain is disabling. It is seen in all ages of people.^1^ It encompasses conditions such as low back pain, neck pain, fibromyalgia, osteoarthritis, pain from fractures or other rheumatological diseases. Many people have more than one body region affected.^2^ It affects approximately 17 million people in the UK, with 9.1 million people living in England with long-term back pain.^3^ National Health Service (NHS) costs to treat musculoskeletal diseases are in excess of £5 billion per year.^3^

People with chronic musculoskeletal pain frequently have difficulties in managing their symptoms and everyday activities to maintain independence and quality of life.^4^ To assist with symptoms, they often access support. This may include help in tasks such as: washing and dressing, preparing meals and assistance in feeding, housework or shopping.^5 6^ This caregiving may be formal or informal. Formal care is defined as the provision of care by someone who is paid. Informal care is provided without a direct payment. This is often given by a spouse or partner, family members and/or friends.^7^

Being a caregiver for someone with chronic musculoskeletal pain can be a physical and emotional burden.^8^ Becoming a caregiver in this situation can significantly change the dynamic of a relationship with feelings of burden which can lead to resentment,^9^ changing roles and identities not only between the patient–caregiver dyad but also impacts on family, social and occupational life, and fear and concern regarding the future and how chronic pain may impact on the individual they support, over-time.^9 10^ Usual NHS care is focused on the patient, providing interventions to support the long-term management of pain and disability. These are either through structured programmes such as the ESCAPE-Pain programme,^11^ or non-structured guidelines incorporating elements of education, exercise, pain relief and psychological interventions.^12–14^ In both instances, none of these approaches has included caregiver interventions to support symptom management.

No caregiving interventions have existed to address the health and social needs of people with chronic musculoskeletal pain or to support caregivers. In response, the research team developed the JOINT SUPPORT programme. This is aimed to improve patient symptom management by educating, supporting and empowering caregivers to optimise the support they give their family member or friend with chronic musculoskeletal pain.

Caregiver interventions, in principle, improve the health and well-being of patients and their caregivers through better self-management skills.^9^ This is important as living with pain is associated with a negative health status, including reduced independence, social isolation and loneliness, obesity and comorbidities associated with physical inactivity such as type 2 diabetes, depression and cardiovascular disease.^15–17^ Improving the skills, capability, motivation, confidence and knowledge so that people with chronic musculoskeletal pain can better manage their symptoms could reduce demand on NHS services through improved self-management and wider health improvement.

### Aim and objectives

#### Aim

To assess the feasibility of conducting a pragmatic, multicentre, randomised controlled trial (RCT) to test the clinical and cost-effectiveness of an informal caregiver training programme to support people with chronic musculoskeletal pain.

#### Objectives

The main objectives are to assess the:

Feasibility of recruiting eligible patient and caregiver dyads in the NHS.Acceptability of the JOINT SUPPORT programme to caregivers, patients and healthcare professionals.Fidelity of delivery of the JOINT SUPPORT programme by healthcare professionals.Ability of caregivers to deliver components of the JOINT SUPPORT programme with fidelity, confidence and competency to patients at home.Acceptability of caregiving dyad randomisation for patients, caregivers and healthcare professionals.Risk of intervention contamination when experimental and control groups are delivered in the same setting.

The secondary objectives are to assess the:

Completeness of outcome measure data.Signal of the clinical effectiveness of the JOINT SUPPORT programme.

## Methods and analysis

This trial builds on previously performed caregiver intervention methods undertaken by the research team.^18^

### Trial design

A mixed-methods feasibility study comprising of a parallel, multicentre, pragmatic RCT and embedded qualitative study. Figure 1 illustrates the study flow.

**Figure 1 F1:**
[figure not shown]
Study flowchart illustrating the participant flow for the JOINT SUPPORT study. NHS, National Health Service.

Prior to commencing, all participating site team members will be taught the skills and knowledge required to fulfil their delegated role in the trial. They will have completed training, including Good Clinical Practice (GCP)^19^ if required. Their participation and competence in delegated roles will be recorded in a site delegation log.

### Eligibility

We will include:

Patients aged 18 years and over with a history (6 weeks or more) of pain from a musculoskeletal (bone, joint or muscle) origin who have a current referral to, or who are attending physiotherapy, rheumatology, orthopaedic, occupational therapy or pain management services.Patients able to nominate an informal caregiver. An informal caregiver is defined as someone who has done or is expected to provide unpaid care, assistance, support or supervision in activities of daily living for at least 3 hours per week over two or more personal contacts.Patients and caregivers willing and able to provide consent.Patients and caregivers who can engage in a group-based intervention currently delivered in English.

If the participating hospital appointment is routinely a virtual appointment rather than in-person, patient and caregiver participants must have access to a device which can receive this. If a patient has multiple caregivers, a single, nominated by the patient, ‘principal’ caregiver will be elected.

We will exclude:

Patients or caregivers with acute (requiring hospitalisation) or terminal illness (life expectancy <6 weeks) which would make participation in the rehabilitation strategies contraindicated and/or impractical.

### Recruitment

Patients will be identified and approached during rheumatology, orthopaedic, pain management, occupational therapy or physiotherapy outpatient appointments. A member of the clinical team will screen participants against the eligibility criteria. This will be recorded on the site screening log. For eligible participants, a member of the site clinical team will briefly outline the study and offer a recruitment information pack. The pack includes: covering letter, Participant Information Sheet (PIS, separate for patient and caregiver), consent form (patient and caregiver), baseline questionnaires (separate for patient and caregiver), participant contact details form (separate for patient and caregiver) and demographic characteristics form (patient and caregiver) with a prepaid envelope. With this information, potential participants will be asked to consider participation. If a caregiver is present with the patient at the appointment, they will be provided with the caregiver PIS. If not, the patient will be provided with this to give to the caregiver. The potential patient and caregiver participant will be asked to read this information. After a minimum of 24 hours, each participant provided with the recruitment information pack will be telephoned or video-called by the site team member and provided with an opportunity to ask questions. They will be informed that if they would like to participate, they should complete the consent form, and then (sequentially) participant contact details form (patient and caregiver) and demographic characteristics form (patient and caregiver) and baseline questionnaire (patient and caregiver) and to return them using the prepaid envelope to the central trial team, who will then randomise the participant-dyad and notify the site team of both enrolment and group allocation. We will aim to recruit potential patient and caregiver participants within 14 days of the initial contact.

All screening activity will be recorded by a member of the trained local site team using the trial’s screening log. Eligible participants who are approached but who do not wish to participate will be anonymously recorded as part of a screening log, providing information on: age, gender, date of appointment and type of musculoskeletal pathology.

Both caregiver and patient consent will be required.

### Randomisation, blinding and allocation concealment

Randomisation will take place once patient and caregiver participant consent forms and baseline questionnaire packs have been completed, received and checked by a member of the central trial team at Norwich Clinical Trials Unit (NCTU). The randomisation scheme will be generated by the NCTU Trial Manager and the allocated group will be notified by email to the site trial team. Randomisation will be stratified at the individual-dyad level (approximately 2:1) by:

SiteAge of patient (< or > and equal to 65 years).

The allocation is computer generated so will not be known prior to randomisation. Allocation is concealed prior to randomisation to prevent selection (or treatment allocation) bias.

Due to the participatory nature of rehabilitation, it will not be possible to blind patients, caregivers or treating healthcare professionals to group allocation after randomisation. The trial PIS has presented intervention equipoise. Therefore, while not possible to blind, we have aimed to limit expectation bias through careful selection of PIS wording for participants.

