#### Support patients and caregivers to increase capability, set targets and monitor goals to facilitate patients improved symptom management

Patients with chronic musculoskeletal pain in an outpatient setting (CONTEXT) will be supported by caregivers to set personalised shared goals which they can realistically meet (MECHANISM) to facilitate improved functional, health-related outcomes and increased independence (OUTCOME).

Participants randomised to the JOINT SUPPORT programme will receive usual NHS treatment (control group intervention as detailed below) PLUS five, 1-hour, group-based training sessions, delivered by a study-trained physiotherapist or occupational therapist. The intervention will be delivered through two possible approaches.

Approach 1: Face-to-face delivery which will be group-based, consisting of a target of three to five dyads in each class. They will be delivered in an outpatient setting provided to both participants in the dyad by a study-trained physiotherapist or occupational therapist.

Approach 2: Video consultation if face-to-face consultations are not permitted within a participating NHS organisation, group-based video consultation sessions using an NHS authorised platform will be used to deliver the content of the JOINT SUPPORT programme as per the face-to-face delivery approach.

If there is a change in service delivery once a participant-dyad has started their JOINT SUPPORT programme, switching from Approach 1 to Approach 2 will be permitted, with the effects explored in the qualitative substudy.

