### Data analysis

#### Sample size

In total, 80 participant dyads (80 patients/80 caregivers) will be recruited. This sample size will be sufficient to answer our feasibility objectives and assess the a priori progression criteria (table 2).^32^ This number will also allow each site to test the JOINT SUPPORT programme in at least two complete cycles. This sample size follows recommendations^33^ for designing feasibility trials that aim to detect a small–medium standardised effect size (where the definitive trial will be designed with 80% power and two-sided 5% significance).^32 34^

**Table 2 T2:** Feasibility study stop–go, traffic light, progression criteria

	Green (go)	Amber (amend)	Red (stop)
Recruitment	>30% of the patients screened across the sites in 12 months would be eligible	20%–30% would be eligible	<20% would be eligible
Intervention fidelity (healthcare professionals)	>70% of the participant-dyads compliant with their allocated intervention (five face-to-face sessions and booster phone call) as randomised	50%–70% received intervention as randomised	<50% received intervention as randomised
Intervention fidelity (caregivers)	>90% of the participants adopted elements of JOINT SUPPORT programme post-last session	60%–90% adopted JOINT SUPPORT post-last session	<60% adopted elements post-last session
Randomisation acceptability	>40% of the eligible participants consent to be randomised	20%–40% would be randomised	<20% would be randomised
Contamination	<5% of the participants in either group received majority of their allocated treatment cross-over	5%–10% of the participants cross-over	>10% of the participants cross-over
Data collection completion	<15% missing outcome questionnaires for whatever reason at 3-month data collection	15%–30% missing questionnaires	>30% missing questionnaires

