#### Eligibility

The embedded qualitative study is optional for participants. Patients and caregivers will be able to express an interest to be approached regarding the qualitative substudy on the main study consent form at the beginning of the study. The sample will consist of patient–caregiver dyads and physiotherapists and occupational therapists who have delivered the JOINT SUPPORT intervention.

Dyads who have agreed to be contacted for an interview will be purposively sampled to ensure a maximum variation in: age, gender, presenting musculoskeletal pathology, ethnicity, duration of disability, severity of disability (as measured by the baseline MSK-HQ),^22^ relationship of caregiver to patient and duration the caregiver has been caring for the patient. Our intention is for caregivers and patients to be interviewed separately to enable them to more freely express their views but we will interview as a dyad if this is expressly requested.

We anticipate around 24 interviews will be conducted, involving approximately 12 patients/12 caregivers from the JOINT SUPPORT programme and approximately 8 caregivers/8 patients from the TAU group across the sites. Based on our previous research,^9^ this sample size should ensure a range of different viewpoints to reach information power^36^ to answer our feasibility questions.

The healthcare professionals delivering the JOINT SUPPORT intervention will be invited to participate in the voluntary interviews within 3 months of completing one participant through the JOINT SUPPORT programme. A minimum target of one physiotherapist and one occupational therapist who delivered the intervention will be invited to be interviewed from each site (eight participants in total). This will provide a range of contexts from different professional backgrounds. The healthcare professionals will be sent a PIS outlining the objectives and processes involved with this optional substudy. They will be asked to contact the research team by email if they are interested in participating. Those who express an interest will be contacted to arrange a mutually convenient time to conduct the interview.

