The acceptability of the care (both groups)	Would you be happy to talk me through your treatment? As X’s carer, what was your impression of the care. For both of you, what was helpful and less helpful to your care?
Group-based JOINT SUPPORT programme and telephone booster calls (experimental group)	How far did you find the JOINT SUPPORT programme helpful—for both of you. Can you give specific examples? What didn’t work as well? Did you get the telephone calls from the trial team? Can you remember what you talked about? Can you give specific examples of what was helpful, and l helpful? Was there any advice that confused you or you weren't clear about?
What the strengths of the experimental intervention (perceived effectiveness)	What were the most helpful/good-bits of your JOINT SUPPORT intervention? What was good about it What didn’t you like about it?
What the weaknesses of the experimental intervention	What were the less helpful/worse bits of the JOINT SUPPORT intervention?
What modifications they may recommend to interventions received (standard care and experimental groups)	What could we improve? (prompt: What do you think is lacking?) How do you think we could better support you and your carer to support you with chronic pain?
The risk of intervention contamination between the groups	Did you talk to any other patients or caregivers while in hospital about the intervention? Was there any discussion between those who received it and did not receive it?
The ease and convenience of the data collection processes (baseline and 3 months) (all participants)	As you were part of a trial, we had to collect a lot of measurements. Can you talk me through what these were? How easy were they? How convenient were they? Overall, do you have any points to make about the testing?
Applicability of the methods and measures used	How did you manage with the questionnaires we gave you at the start of the study and at the end in the post? Were they easy to complete or do you remember them being a problem?

**Table 4 T4:** Interview topic guide for the healthcare professional interviews

The interview will be structured on the following areas of interest	Sample questions
Introduction (Perceived effectiveness)	Overall, could you share your experiences of being involved with our research?
The randomised to either group	How did you feel about 50% of the patients not receiving the JOINT SUPPORT intervention but getting normal care? Did this ‘sit easy’ with you?

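### The randomisation section allocates about 2:1 without naming the larger arm, but the therapist interview guide says half of patients do not receive JOINT SUPPORT

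*Protocol article*

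**What the plan says.** Four places in the protocol article bear on the allocation.

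- **Randomisation, blinding and allocation concealment.** "Randomisation will be stratified at the individual-dyad level (approximately 2:1) by" site and patient age (under 65, or 65 and over). This is the only design statement of the ratio. The order of the arms is not given.
- **Qualitative study, Data collection, Table 4.** Under the randomisation topic, the sample question for healthcare professionals is "How did you feel about 50% of the patients not receiving the JOINT SUPPORT intervention but getting normal care".
- **Sample size.** "In total, 80 participant dyads (80 patients/80 caregivers) will be recruited". The text gives no split by arm. It adds: "This number will also allow each site to test the JOINT SUPPORT programme in at least two complete cycles".
- **Qualitative study, Eligibility.** The planned interviews are described as "involving approximately 12 patients/12 caregivers from the JOINT SUPPORT programme and approximately 8 caregivers/8 patients from the TAU group".

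The abstract and the trial design section give no ratio. The dyad topic guide (Table 3) asks how allocation felt but states no share, so the 50% figure appears only in the therapist guide.

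**The concern.** A 2:1 allocation cannot leave half the patients on usual care, and the word "approximately" cannot stretch it to 1:1. Both statements are current text, and nothing visible reconciles them.

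The main consequence is in the qualitative work. Acceptability of randomisation to patients, caregivers and healthcare professionals is one of the main objectives, and the assessment section names qualitative interviews as one of its sources. If 2:1 is the true ratio, a therapist asked the Table 4 question as written is invited to comment on an allocation that did not happen. How comfortable a therapist feels about withholding the programme may well depend on whether a third, a half or two thirds of patients go without it. Answers given on a wrong premise cannot be repaired afterwards.

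If 1:1 is the true ratio, the interview question is sound and the error lies in the randomisation section, the one place a reader would look for this figure.

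The missing direction adds to the problem. With no favoured arm in the text and no target arm sizes, a reader has nothing with which to settle the conflict.

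**Working it through.** **Inputs.** Total of 80 dyads (Sample size). Ratio about 2:1, direction not stated (Randomisation). 50% without JOINT SUPPORT (Table 4). Three to five dyads per class (Approach 1 of the intervention). At least two cycles per site (Sample size). Number of sites: not stated. Four is inferred from the qualitative Eligibility section, where one physiotherapist and one occupational therapist per site make eight in total (8 / 2 = 4). Equal recruitment across sites is assumed.

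**The plan's own figure.** The total of 80 cannot be rebuilt from the text. The section names a small to medium standardised effect without a number, and the power statement, "where the definitive trial will be designed with 80% power and two-sided 5% significance", describes the later trial. For illustration, n per arm = 2(1.96 + 0.84)² / d² with assumed d of 0.2, 0.3 and 0.5 gives 393, 175 and 63. None of these is meant to equal 80, and nothing here shows 80 to be wrong.

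**Step 1: share without JOINT SUPPORT.** At 2:1 towards JOINT SUPPORT it is 1/3 = 33%. At 2:1 towards usual care it is 2/3 = 67%. At 1:1 it is 50%. Only 1:1 fits Table 4.

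**Step 2: arm sizes.** 80 × 2/3 = 53.3 and 80 × 1/3 = 26.7, so about 53 and 27. At 1:1 they are 40 and 40.

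**Step 3: cycles per site** = (JOINT SUPPORT dyads / 4) / dyads per class.

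| JOINT SUPPORT arm | Dyads per site | Classes of 5 | Classes of 4 | Classes of 3 |
|---|---|---|---|---|
| 53 | 13.25 | 2.65 | 3.31 | 4.42 |
| 40 | 10 | 2.0 | 2.5 | 3.33 |
| 27 | 6.75 | 1.35 | 1.69 | 2.25 |

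Two cycles are reached at every class size with 53 or 40, but only with classes of three at 27. The statement therefore counts against 2:1 towards usual care and does not separate 53 from 40.

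*Range for the site assumption.* The abstract speaks of 12 professionals. At two per site that would be six sites, and 27 / 6 / 3 = 1.5 cycles, so 27 would fail even with classes of three. Between the other two, 40 / 6 / 3 = 2.2 and 53 / 6 / 3 = 2.9, so both still pass with classes of three.

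**Step 4: between-group precision.** The 95% CI half-width in SD units is 1.96 × √(1/n₁ + 1/n₂).

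- 2:1, either direction: 1.96 × √(1/53 + 1/27) = 1.96 × 0.236 = 0.463.
- 1:1: 1.96 × √(2/40) = 1.96 × 0.224 = 0.438.
- Ratio 0.463 / 0.438 = 1.06, so the interval is about 6% wider.
- With 15% missing, dividing each by √0.85 gives 0.503 and 0.475.

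**Step 5: within-arm precision.** For fidelity at the 70% threshold the half-width is 1.96 × √(0.7 × 0.3 / n): 12.3 points at n = 53, 14.2 at n = 40 and 17.3 at n = 27. Compared with 1:1, a 2:1 ratio towards JOINT SUPPORT improves this estimate; the opposite direction worsens it.

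**Step 6: does the interview split settle it?** 12 to 8 dyads is 3:2, which matches neither ratio. The sample is purposive, so it does not indicate how dyads are randomised.

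**The case against.** The two statements do not have equal standing. The randomisation section is the design statement. The 50% sits in a column of sample questions for a semi-structured interview, and changing it would not alter how any dyad is allocated. A drafting slip in the prompt is a natural explanation. In addition, the flowchart (Figure 1) is not visible here and the full protocol is not shown, so either may name the larger arm or give its size. This stands, and it limits the point to what the visible text says. It does not remove the contradiction, because an article may leave detail to a fuller document but should not carry two incompatible ratios.

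Four stronger readings are tempting, and the documents do not support them.

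- *That the fidelity, adoption and contamination criteria lose their denominators.* Those proportions will be taken over the dyads actually allocated. The thresholds do not depend on a planned ratio, and the progression section treats them as a guide, with unmet criteria going to the oversight committee.
- *That precision is seriously harmed.* The widening is about 6%, the analysis is descriptive and no formal testing is planned.
- *That consent to a 2:1 offer would not carry over to a 1:1 definitive trial.* The article nowhere says the definitive trial will be 1:1.
- *That expected CI widths should have been given.* A condensed article commonly leaves these to the full protocol.

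**Conclusion.** The inconsistency is real: 2:1 in the randomisation section and 50% in Table 4 cannot both describe this trial. The visible text does not settle which is right. It supports three readings of the JOINT SUPPORT arm (53, 40 or 27 of 80). The two-cycle statement makes 27 unlikely, on the assumption of four sites recruiting equally.

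The size is minor to moderate. What lifts it above a typing error is that the allocation ratio is a core design figure and that, under 2:1, the therapist question would carry a false premise into a main objective. A reader might infer that 2:1 is an unsound choice or that 80 is the wrong total; neither is shown. The conclusion depends on the visible text only, and a clear statement in Figure 1 or the full protocol would answer the question of direction but would still leave the article's text to be reconciled.

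**What to change.** 1. In the randomisation section, state one ratio and name the arms in order.
2. In the sample size section, give the resulting target arm sizes beside the total of 80 dyads (53 and 27 in the stated direction, or 40 and 40).
3. In Table 4, replace the 50% with the true share of patients not receiving JOINT SUPPORT, or remove the figure from the question.

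The cost is wording only. No change to the sample size, analysis or progression thresholds is needed. The Table 4 correction has a deadline: it must be made before the first healthcare professional interview. If interviews have already used the 50% wording and the ratio was 2:1, say so when those answers are reported.
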